### Research aims

This study involves an effect evaluation (RCT) and a process evaluation (qualitative research) of SEd. The first question that will be addressed is:
A)What is the effect of the SEd intervention on remaining at school (primary outcome), study success and student satisfaction (secondary outcomes) of students with mental health problems who follow post-secondary education, as compared to students with mental health problems who receive support as usual plus advice from a trained educational staff member on potential supportive resources?

We plan to test the following hypotheses:
More students who receive the SEd intervention will remain at school or graduate as compared to students who receive support as usual plus advice on potential supportive resources.Students who receive the SEd intervention will be more successful at school, operationalized as a higher GPA and a higher number of credits and courses completed, than students who receive support as usual plus advice on potential supportive resources.Students who receive the SEd intervention will experience a higher level of satisfaction at school than students who receive support as usual plus advice on potential supportive resources.

The second research question that will be addressed is:
B)What are the essential components of the SEd intervention according to students and SEd specialists?

## Methods/ design

### Design

This study uses a mixed methods design that combines quantitative research (RCT) with qualitative research (monitoring, interviews, focus groups), including an intervention condition and an active control condition. The students in the intervention condition receive the SEd intervention, the students in the active control condition receive support as usual plus advice from a trained educational staff member on potential supportive resources regarding studying with mental health problems.

### Participants

Study participants are students with mental health problems who want to complete their current education studying at Mbo Utrecht, which is an educational institute that provides post-secondary vocational education, or at the Hanze University of Applied Sciences Groningen, an educational institute for higher professional education. They will be recruited through personal contact with educational professionals, information brochures (see Additional file 1), posts on the internal website of the schools, posters and social media. Inclusion criteria are:
having a mental health condition (e.g. depression, anxiety disorder, bipolar disorder, psychosis, ADHD) for which the student has received a formal diagnosis or the student experiences symptoms for at least 6 months, and;receiving treatment for mental health problems or having received treatment in the past, and;being at least 16 years of age, and;following regular post-secondary vocational education in Utrecht; or higher education in Groningen, and;expressing the need for extra support to remain at school.

Exclusion criteria are:
not fluently speaking and reading in Dutch, or;the need for extra support is only expressed by others than the student, or;unable to give informed consent, or;less than six months to go before graduation, or;has received SEd services in the past

### Sample size calculation

As mentioned before, this is the first RCT on the effect of our SEd intervention on remaining at school, our main outcome measure. Therefore, the effect size of our intervention on remaining at school is unknown. In such cases, it is a common convention to set the effect size at 0.5 [35], because a lower effect size would not be considered as clinically relevant [36, 37]. Therefore, we aim to demonstrate an effect size of 0.5 on the primary outcome measure remaining at school with a power of 80% and an alpha < 0.05.

Hence, for each condition 51 students are needed (total 102). Given an expected drop-out percentage of 25% from the study, 140 students (2 × 70) need to be included in the study. This is a feasible number, considering that 20–45% of students worldwide experience mental health problems [1, 38, 39].

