## Background

Over the past decade, an increase in mental health problems is seen among students in post-secondary education worldwide and these mental health problems are found to negatively influence the educational goals of these students [1–7]. For instance, having mental health problems increases the risk of dropping out of vocational and higher education up to twice as high [8–11]. For example, in the study of Hjorth et al. [9], the dropout rate amongst students with mental health problems was approximately 15% after five years, compared to a dropout rate of 8% in students without mental health problems. In an economy that requires (higher) education for upward occupational mobility, people who are unable to succeed in post-secondary/higher education or training may find themselves ultimately underemployed or unemployed [12–14]. Therefore, it is of the utmost importance to support students with mental health problems to complete their studies. Supported Education could be the support that is needed to reach that goal.

Supported Education (SEd) is defined as the provision of individualized, practical support and instruction to assist people with mental health problems to choose, get and keep their educational goals [15–18]. The mission of SEd is derived from the choose-get-keep model of the Boston Psychiatric Rehabilitation Approach (PRA): To help people with mental health problems develop the skills and supports required to be successful and satisfied in their chosen roles or environments [15, 19].

A SEd toolkit, based on this choose-get-keep model of psychiatric rehabilitation has already been developed to support students with mental health problems to return to or to remain at school. This toolkit provides tools and guidelines for organizations and professionals working with people with mental health problems [20]. In a small pilot project, the ‘keeping phase’ of the toolkit has been tested among eleven professionals and eleven students with mental health problems who follow post-secondary education [21]. The goal of the ‘keeping phase’ is to remain at school and increase study success and student satisfaction through the development of skills and support. The first results were positive: professionals indicated that the tools were useful, concrete and user-friendly; the students indicated that they felt more supported, got higher grades, and that their school functioning in general improved.

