With respect to the primary outcome, remaining at school, we will compare the number of students who remained in education or graduated in the experimental and the control condition at T2. Logistic regression models will be conducted to test the differences between the experimental and control condition. In addition, the differences in scores on the secondary outcomes, study success and student satisfaction, will be examined for T0 to T2 using chi squares or repeated measures of variance with the ANOVA test using 95% confidence levels, respectively. Furthermore, the differences between the two conditions on number and duration of contacts with the SEd specialist, the trained staff member or students service provider; the number of study skills where the students need support with and the number of resources needed or used when studying, student general self-efficacy levels and the working alliance with the professional, will be calculated using the ANOVA test with 95% confidence levels. Moreover, to test whether outcomes are similar for students from both educational institutions, sensitivity analyses will be performed excluding students from the institute for intermediate vocational education.

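### The 51 per arm needs a one-sided test that is never declared and an effect size of 0.5 that is undefined for a yes/no outcome; two-sided, 51 per arm gives about 71% power, not 80%

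*Protocol article*

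**What the plan says.** The section Sample size calculation states that the effect on remaining at school is unknown and that "it is a common convention to set the effect size at 0.5", "because a lower effect size would not be considered as clinically relevant". It then sets the target, an "effect size of 0.5 on the primary outcome measure remaining at school with a power of 80% and an alpha < 0.05", and draws from it that "for each condition 51 students are needed (total 102"). Allowing for 25% study drop-out, it plans 140 students, 70 per condition.

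The section Primary study outcomes defines the outcome as a dichotomy: still at school or graduated, versus dropped out. For its analysis at 12 months, Proposed analyses says "Logistic regression models will be conducted to test the differences between the experimental and control condition". Research aims words the hypothesis in one direction: "More students who receive the SEd intervention will remain at school or graduate".

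The only school drop-out rates in the article are in the Background, from one cited study: "the dropout rate amongst students with mental health problems was approximately 15% after five years, compared to a dropout rate of 8" per cent in students without such problems.

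**The concern.** Three things in the sample size statement do not fit together.

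- The usual reading of a 5% alpha is two-sided, and two-sided the stated inputs do not give 51.
- The figure 0.5 has no unit. For a proportion it could be Cohen's h, a converted odds ratio or something else, and these differ greatly in what they ask of the intervention.
- The article calls anything below 0.5 not clinically relevant, although the drop-out gap that it uses to motivate the trial may lie well below that.

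At stake is how the primary result will be read. If the trial is taken to have 80% power for every effect that matters, a non-significant result will be taken to mean that no relevant effect exists. That inference needs a power statement that holds for the test and the outcome actually used.

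**Working it through.** **Inputs.** From Sample size calculation: effect size 0.5 (no metric), power 80%, alpha 0.05 (sides not stated), 51 per arm, 25% study drop-out, 70 per arm planned. From Background: 15% and 8% drop-out over five years. Control retention at 12 months is not given, so a range is assumed below.

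**1. Reproducing 51.** Normal approximation for a standardised difference, per arm: n = 2(z_alpha + z_power)² / 0.5².

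| Test | Normal approximation (also Cohen's h) | t-test (noncentral t) |
|---|---|---|
| One-sided 5% | 2(1.645 + 0.842)² / 0.25 = 49.5, so 50 | 50.15, so **51** |
| Two-sided 5% | 2(1.960 + 0.842)² / 0.25 = 62.8, so 63 | 63.77, so 64 |

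The inflation is in order: 102 / 0.75 = 136, rounded up to 140.

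**2. Power for 0.5.** Power = Φ(0.5·√(n/2) − z_alpha).

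- 51 per arm, one-sided: Φ(2.525 − 1.645) = 81.1% (t-test 80.6%).
- 51 per arm, two-sided: Φ(2.525 − 1.960) = 71.4% (t-test 70.6%).
- 70 per arm, two-sided: Φ(2.958 − 1.960) = 84.1% (t-test 83.6%).

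**3. What 0.5 means on the binary outcome.** If it is Cohen's h, h = 2·arcsin√p_T − 2·arcsin√p_C, so p_T = sin²(arcsin√p_C + 0.25). The powers below come from exact enumeration of the pooled chi-square test, which stands in for an unadjusted logistic regression.

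| Control retention (assumed) | Target retention at h = 0.5 | 51 per arm, one-sided | 51 per arm, two-sided | 70 per arm, two-sided |
|---|---|---|---|---|
| 50% | 74.0% | 81% | 72% | 84% |
| 60% | 82.3% | 82% | 71% | 84% |
| 75% | 92.7% | 80% | 70% | 84% |
| 85% | 97.8% | 82% | 68% | 84% |
| 90% | 99.5% | 81% | 64% | 81% |

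From 95% control retention the largest possible h is π − 2·arcsin√0.95 = 0.45, so h = 0.5 cannot be reached. The pooled normal formula is more pessimistic near the boundary: at 85% it gives 64% for 51 and 78% for 70 per arm.

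If instead 0.5 is a standardised difference converted to an odds ratio, exp(0.5π/√3) = 2.48. That takes 85% to 93.3%, with two-sided power of 27% at 51 and 36% at 70 per arm.

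**4. A smaller effect, as an illustration.** Assume retention of 85% versus 92%, borrowing the two Background rates. Then h = 2.568 − 2.346 = 0.22, less than half of 0.5.

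| Per arm | Two-sided | One-sided |
|---|---|---|
| 51 | 19% | 29% |
| 70 | 25% | 37% |

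Under other assumptions, a ten-point gain from control retention of 50 to 75% has two-sided power of 17 to 24% at 51 and 22 to 31% at 70 per arm (pooled formula).

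**The case against.** The best defence is that 51 is a legitimate one-sided calculation. The hypothesis is directional, and Cohen's h, an effect size made for proportions, gives 50 per arm one-sided. At 51 per arm the exact one-sided power is 80 to 82% across control rates. This stands so far: a reader might infer that 51 fits only a t-test on a continuous outcome, or that it cannot give 80% power for a binary one, and neither is supported. What does not follow is that a directional hypothesis declares a one-sided test.

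A reader might also cite the 95% confidence levels in Proposed analyses as proof of a two-sided plan. There they belong to the analyses of secondary and exploratory measures, not to the logistic regression. The fault is undeclared sidedness, not a proven contradiction.

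Second, the trial plans 70 per arm, and Proposed analyses and the Discussion expect primary outcome data from school records even after study drop-out. Two-sided power for h = 0.5 is then about 81 to 84%. This also stands, provided that 140 are enrolled. The Abstract speaks of one hundred, and at 50 per arm two-sided power for 0.5 is about 70%.

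Third, the Background rates are not design rates. They cover five years and compare students with and without mental health problems. The trial compares two kinds of support at 12 months, in students who ask for help to stay at school. A reader might infer that the trial has only 20 to 25% power. The documents do not support that as a statement about this trial; it is one scenario.

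**Conclusion.** The concern holds in a limited form. The stated 51 per arm at 80% power requires a one-sided 5% test that the article does not declare. Under a two-sided test it needs 63 to 64 per arm, and 51 gives about 71% (64 to 72% by exact test for h = 0.5, over assumed control retention of 50 to 90%). Independently of sidedness, 0.5 has no defined meaning on the primary outcome, because neither a metric nor any retention rate is given.

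The planned enrolment largely absorbs the two-sided shortfall, if 0.5 means h and all 70 per arm are analysed. It does not cover modest effects. For 85% versus 92%, power stays at or below 37% at 70 per arm, whether one-sided or two-sided.

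The relevance claim is the other weak point. On the h scale, removing the entire excess drop-out cited in the Background (h = 0.22) would count as not clinically relevant. This last step assumes that 0.5 is h, which the article does not say.

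**What to change.** Rewrite Sample size calculation without enrolling more students:

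1. Declare a two-sided 5% test for the primary outcome.
2. Replace the unit-free 0.5 by explicit control and target retention percentages, over a stated range of control rates.
3. Replace the claim of 80% power at 51 per arm by the two-sided power at the number to be analysed from school records (70 per arm if 140 are enrolled; bring the Abstract's one hundred into line). Show the lower power for smaller differences as a labelled range, and mark any use of the five-year rates as illustrative.
4. Drop or qualify the statement that an effect below 0.5 is not clinically relevant.

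The cost is wording only. The downside is that the stated power becomes less favourable for modest effects. Reporting a risk difference with its confidence interval would fit this restatement, but that is a reporting choice and not needed to correct the error.

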### Study procedures

We adhere to the SPIRIT 2013 guidelines [40], the checklist is provided in the Additional file 2.

Students who heard about the study through one of the recruitment strategies and are interested in participation, contact the research team by e-mail. A data coordinator will check the inclusion criteria and will then send a link to an online questionnaire which starts with information about the study and the question to fill out an informed consent form. In the informed consent (see Additional file 3), students state that they have been informed about the study and that they participate voluntarily. In addition, they give permission to collect grades and course credits from the school’s administration for the next five years, so we are able to follow the study success of the students after the current project has finished. They also give permission that in case they drop-out of the study, school progress keeps being monitored. Students have the right to withdraw this permission at any moment in time.

After signing the informed consent, the students fill out the baseline-questionnaire. Then, students will receive a student ID number and will be randomized, for both educational institutes separately, by the data coordinator in either the experimental condition (Supported Education-coaching; half of the group of students) or the control condition (support as usual plus advice on potential resources; half of the group of students), using the minimization approach [41] which aims to minimize imbalance between the conditions on specific factors, in our case on gender, age, ethnicity, study year, level of study, the number of credits completed, and level of psychological distress. The condition to which the student is allocated depends on the characteristics of the students that were already enrolled. Students will receive compensation (a gift coupon of 12,50 euro each) for filling in the questionnaires at baseline, 6- and 12-month follow-up. Within this 12-month follow up, each student experiences a critical moment in the educational pipeline: either transitioning to the next year or graduating. In Table 1, the Spirit flow diagram of the study procedure is presented.

**Table 1 Tab1:** SPIRIT flow diagram of the study procedure showing enrolment, interventions, and assessments

	Pre-intervention	Post-intervention (within one month)	6 month follow-up	12 month follow-up
**TIMEPOINT**	**t**_**0**_		***t***_***1***_	***t***_***2***_

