**Fidelity**				
*Interview*			X	

The quantitative data will be collected online for both sites by the data coordinator using online questionnaires through Enalyzer (a secure software program for research purposes). The data in Enalyzer will be linked to the student ID for this study so that the answers are not linked to identifiable information. All data will be handled confidentially in compliance with the Dutch Personal Data Protection Act (Wet Bescherming Persoonsgegevens; WBP). All data will be stored and locked at the Hanze University of Applied Sciences Groningen and will be destroyed ten years after finishing the study.

Students are blinded for which type of intervention is the experimental/control intervention. They are told that we will compare two types of support services of which they will receive one. The data coordinator who will perform the randomization process is obviously not blinded as is the researcher who will conduct the interviews about the support with the students afterwards. However, they have no personal interest in the outcomes.

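### Eligibility and minimisation rest with the same unblinded data coordinator, and the only safeguard given, lack of personal interest, does not conceal the next allocation

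*Protocol article*

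**What the plan says.** Study procedures sets out the sequence. An interested student e-mails the research team. Then "A data coordinator will check the inclusion criteria and will then send a link to an online questionnaire". Consent and the baseline questionnaire follow. After that, students "will be randomized, for both educational institutes separately, by the data coordinator", in a 1:1 split, "using the minimization approach [41] which aims to minimize imbalance between the conditions on specific factors". The factors are "gender, age, ethnicity, study year, level of study, the number of credits completed, and level of psychological distress". On the rule itself the article adds: "The condition to which the student is allocated depends on the characteristics of the students that were already enrolled".

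The text after Table 1 gives the same role the online collection of the quantitative data for both sites. It then states: "The data coordinator who will perform the randomization process is obviously not blinded". The interviewing researcher is also unblinded, and the reassurance offered for both is: "However, they have no personal interest in the outcomes".

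The article describes no step that keeps the upcoming allocation from the person who decides on eligibility.

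**The concern.** Blinding and allocation concealment are different protections. Blinding concerns what is known after assignment. Concealment concerns what can be known or guessed before a student is accepted. The article treats the coordinator's knowledge as a blinding matter and answers it with a statement about motive. That does not stop someone who knows the earlier allocations from anticipating the next one, and selection at entry need not be deliberate.

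There is some room for selection. Under Participants, the six-month symptom route, the student's own need for support and fluency in Dutch rest on self-report or judgement. Motivation and dropout risk are not minimisation factors. If admission leaned on them in the light of the likely arm, the arms would differ on something that bears directly on remaining at school. Proposed analyses adjusts for observable characteristics only. Taking the primary outcome from school records protects its measurement but not the comparability of the arms at entry.

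The trial is small. With 70 students per condition (Sample size calculation), one student is 1/70 = 1.4 percentage points of the primary outcome and five are 5/70 = 7.1 points. For scale only: the Background cites five-year dropout of about 15% with mental health problems and 8% without, a gap of 7 points.

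**Working it through.** The article gives no figure on this point, so there is none to reproduce. The check has a textual part and an illustrative part.

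**1. Roles and order, from Study procedures**

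| Step | Who | What is known by then |
|---|---|---|
| E-mail | research team | not described |
| Inclusion check, link sent | data coordinator | whatever the contact reveals; no questionnaire yet |
| Consent, baseline questionnaire | student | distress score and other baseline answers now exist |
| Minimisation | data coordinator | baseline data; earlier allocations must enter the rule |

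Screening and allocation therefore lie with one role. Screening comes before the questionnaire, so prediction at screening works with fewer factors than prediction just before allocation.

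**2. How predictable is the next arm?**

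Inputs from the article: seven factors, minimisation within each institute, 1:1 allocation.

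Assumptions, not in the article: 2-4 equally likely levels per factor (2, 3, 2, 4, 3, 3, 3 in the order listed), independent factors with equal weights, a coin toss at ties, and 51 or 70 students in an institute. The article's 2 × 70 is per condition; it gives no number per institute. The number hardly matters: results for 51 and 70 agree within about one percentage point.

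For a new student, let D_f be the number in arm A minus the number in arm B among earlier students who share the student's level of factor f. The score is d = Σ_f (|D_f + 1| − |D_f − 1|). If d < 0, arm A is preferred; if d > 0, arm B; if d = 0, there is a tie. The preferred arm is assigned with probability p. The guesser knows the earlier allocations and computes the same sum over the factors known at that moment.

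Correct-guess rates from simulation (chance = 50%):

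| Factors known | p = 1 | p = 0.8 | p = 0.7 |
|---|---|---|---|
| gender, level | 71% | 63% | 58% |
| gender, level, study year | 75% | 66% | 61% |
| all but distress and credits | 83% | 70% | 63-64% |
| all but distress | 87% | 72-73% | 65-66% |
| all seven | 92% | 76% | 67% |

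A single known factor gives about 66% at p = 1.

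Hand check with all seven known: rate = (1 − t)·p + t/2, where t is the share of ties.
- p = 1, t = 0.162: 0.838 + 0.081 = 0.919, against 0.921 simulated.
- p = 0.8, t = 0.145: 0.855 × 0.8 + 0.0725 = 0.757, against 0.758 simulated.

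If d is instead the plain sum of the differences D_f, ties fall to about 11% and the all-seven rate at p = 1 becomes 1 − 0.11/2 = 0.945, about 95%.

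**3. Reading the table**

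At screening the distress score does not yet exist and the number of credits may not be known. That gives about 66-83% at p = 1, or 87% if credits are known as well. Once baseline data are in, the figure is 92-95%. A random element lowers these rates but leaves them above 50% as long as the guesser knows earlier allocations. Removing that knowledge from the screener closes this route.

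**The case against.** The strongest reply is that much of this is silence in a condensed article. It says students are randomised, cites a method reference for minimisation and points to a SPIRIT checklist; neither is shown here. The assignment probability is a detail often left to the full protocol. The sentence that allocation depends on students already enrolled is true of minimisation with or without a random element. A reader might infer that the scheme is deterministic; the article does not establish that. This part of the objection stands, and the point does not rest on a missing random element.

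A reader might also infer that the coordinator knows the arm when admitting or refusing a student. The order of steps does not support certainty: the questionnaire comes later, so the 92-95% figure does not apply at screening. Nor does the article say that the coordinator receives the e-mails, keeps running tallies, or may reopen an eligibility decision. Access to earlier allocations is a reasonable inference from the task of allocating, but it remains an inference.

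Finally, discretion is limited. Students refer themselves, time to graduation is largely factual, and current or past treatment is required in addition to a diagnosis or symptoms. That narrows the room for selection without closing it.

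What the objection does not reach is the stated arrangement: one role, acknowledged to be unblinded, screens and allocates, and the protection offered concerns motive.

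**Conclusion.** The concern holds in this form: the article gives eligibility checking and minimisation to the same unblinded role, and its only stated safeguard does not conceal allocation. Prediction of the next arm would be about 66-83% correct at screening and 92-95% after baseline. These figures are illustrative. They assume that the earlier allocations are known to the person screening, that no random element is used, and that the factor levels, weights and imbalance rule are as set out above. With p = 0.8 the rates are lower (63-70% for two to five known factors, 76% for all seven) but still above chance.

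Nothing here shows that biased admission has taken place or would take place, and the size of any effect on the primary outcome cannot be derived from the document. The point is that the described procedure does not prevent it, and that the planned adjustment would not correct selection on unmeasured characteristics. It should be addressed, given how little the remedy costs.

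**What to change.** 1. Have an existing team member who does not screen run the minimisation and hold the allocation record, so that the person judging eligibility does not see earlier allocations.
2. Log each eligibility decision, covering inclusion and exclusion criteria and including refusals with reasons, and lock it before allocation with no reversal afterwards. Eligibility already precedes allocation in the described order; the recording and locking would be new.
3. Only if the minimisation is in fact deterministic: assign the preferred arm with probability below 1, for example 0.8. This supplements the first two changes and does not replace them.

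The cost is a protocol sentence, a task moved within the team and a short screening log. The third change is one setting in the procedure and slightly loosens balance on the seven factors. If such safeguards already exist in the full protocol, stating them closes the point. If enrolment is already complete, the trial report can list screening refusals with reasons and name the overlap of roles as a limitation.
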